
**Figure 2 figure2:**
[figure not shown]
Schematic representation of remote cardiac rehabilitation in this study. ECG: electrocardiogram.

### Setting of Endpoints

The primary endpoint is the peak oxygen uptake 2-3 months from the start of exercise or 6-min walk test. The secondary endpoints are as follows: indices of cardiopulmonary exercise testing, occurrence rates of clinical events (all-cause deaths, cardiovascular deaths, and cardiovascular hospitalizations), N-terminal fragment of pro–B-type natriuretic peptide (NT-pro BNP) or BNP, health-related quality of life (QOL) scores, daily activity amounts, and questionnaire results. For both groups, various data items will be collected during regular checkups at and 2-3 months after hospital discharge, and improvements in exercise tolerance (peak oxygen intake) will be compared with the occurrence rates of clinical events.

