### RCR Protocol

This study aims to enroll approximately 75 patients introduced to RCR and compare them with patients who received OCR for the same duration as that for a historical control group. The criteria for the control group are as follows: (1) patients who are recommended by the attending physician that they continue postdischarge rehabilitation following in-hospital treatment for diseases indicated for cardiac rehabilitation and (2) those who took cardiopulmonary exercise testing or a 6-min walk test at 2-3 months after discharge.

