### Data Analysis

The analysis will be performed as follows: data on the primary and secondary endpoints of the RCR and control groups will be expressed as mean (SD) or median (quadrant) values. JMP software (SAS Institute) will be used for statistical analysis. Continuous variables will be analyzed using a 2-tailed independent samples *t* test and the Mann–Whitney *U* test. For categorical variables, a chi-square test will be conducted. The RCR group will be compared with the historical control group at the primary and secondary endpoints. The sample size was calculated on the basis of the following estimation. The sample size has been estimated from the data of peak oxygen consumption. A difference in peak oxygen consumption, which is considered clinically relevant, will be in accordance with that reported previously [23,24]. Setting the 2-sided significance level at 5% and power at 80%, a sample size of 67 subjects per group will be required, after allowing for a 40% drop-out rate. Considering these issues, 3 cases are planned to be assigned to each institution (total 75 cases). The level of statistical significance will be set at *P*<.05.

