### Strengths and Limitations

This trial is not randomized and observational; thus, background factors may not be accurately aligned with data on the control group, which will be based on clinical records. Results of exercise capacity is considered the primary outcome; however, the evaluation will be based on the 6-min walk test or a cardiopulmonary exercise test because the cardiopulmonary exercise test cannot be performed at all institutions, and some institutions can only measure exercise capacity by evaluating the 6-min walk test. This inconsistency in the evaluation of exercise capacity might decrease the statistical power of this study. Indeed, the compatibility of data between the cardiopulmonary exercise test and 6-min walk test has not been verified [25]. Laboratory data are measured at each facility, using the method prescribed at each facility, possibly resulting in differences in the laboratory data between each facility. Conversely, increasing the versatility of introducing RCR in this study might facilitate the application of the RCR protocol at various facilities.

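### The primary endpoint is peak oxygen uptake or the 6-minute walk test, with no rule for which counts or how they combine, while the sample size rests on peak oxygen uptake alone

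*Protocol article*

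**What the plan says.** Under Setting of Endpoints: "The primary endpoint is the peak oxygen uptake 2-3 months from the start of exercise or 6-min walk test". The Results paragraph of the Abstract repeats this. The last sentence of Setting of Endpoints then describes exercise tolerance by peak oxygen intake only.

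Strengths and Limitations explains the alternative: cardiopulmonary exercise testing (CPX) is not available everywhere, and "some institutions can only measure exercise capacity by evaluating the 6-min walk test". It adds that "the compatibility of data between the cardiopulmonary exercise test and 6-min walk test has not been verified" and that "This inconsistency in the evaluation of exercise capacity might decrease the statistical power of this study".

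Under RCR Protocol, the second criterion for historical controls covers "those who took cardiopulmonary exercise testing or a 6-min walk test at 2-3 months after discharge", so either test admits a control.

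Under Data Analysis: "Continuous variables will be analyzed using a 2-tailed independent samples *t* test and the Mann–Whitney *U* test". Significance is set at P<.05. On sample size: "The sample size has been estimated from the data of peak oxygen consumption". The result is 67 per group at two-sided 5% and 80% power after 40% drop-out, with 75 remote-rehabilitation patients planned. The target difference and its SD are not given, only a reference to earlier reports: "A difference in peak oxygen consumption, which is considered clinically relevant, will be in accordance with that reported previously".

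**The concern.** A primary endpoint has to identify the single result on which the trial will be judged. Here it names two measures in different units, assigned by site, and does not say which one decides or how they join. The power calculation covers one of them and assumes that every evaluable patient contributes to it.

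Two things are at stake. If success on either test counts, the 5% level is not the real error rate. If only peak oxygen uptake counts, the patients without CPX drop out of the primary comparison and power falls below the planned 80%. Because the comparison is with historical controls, whose results may already exist, leaving the choice open also leaves room to choose after seeing data.

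**Working it through.** **Inputs from the article.** Two-sided 5%, 80% power, 67 per group after 40% drop-out, 75 planned in the remote group (Data Analysis). **Not in the article:** the target difference, its SD, the share of patients with CPX, and the number of controls. Every CPX share below is an assumption.

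**1. The plan's own figure.** It cannot be reproduced directly without the difference and SD, but it can be back-solved. 67 × (1 − 0.40) = 40.2, so 40 evaluable per group; forward, 40 / 0.60 = 66.7, rounded up to 67. From n = 2(1.960 + 0.842)² / d², with n = 40, d = 2.802 × √(2/40) = 0.626 SD (0.634 with the t distribution).

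**2. Reading A: two primary tests, each at 5%, success on either.**
- Independent tests, as when different sites supply each: 1 − 0.95² = 9.75%.
- Correlated test statistics (bivariate normal): 9.1% at correlation 0.5, 8.4% at 0.7, 7.0% at 0.9.
- With each test at 2.5%: n = 2(2.241 + 0.842)² / 0.626² = 48.4, so 49 evaluable. 49 / 0.60 = 81.7, so 82 enrolled per group, against 67 stated and 75 planned, even if every patient had both tests.

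**3. Reading B: peak oxygen uptake only.** If a share f of both groups has CPX, power = Φ(2.802·√f − 1.960). The unknown difference and SD cancel, so this does not depend on the value of d in step 1.

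| Assumed CPX share | Evaluable per group (of 40) | Power | Power if 45 per group (75 × 0.6) |
|---|---|---|---|
| 100% | 40 | 80% | 84% |
| 80% | 32 | 71% | 76% |
| 70% | 28 | 65% | 70% |
| 50% | 20 | 51% | 56% |
| 30% | 12 | 33% | 37% |

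With 40 per group, any share below 100% misses 80%. With 45 in both groups, the share must be about 40/45 = 89%.

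**4. Reading C: raw values pooled (not stated in the article; illustrative only).** Assumed: peak oxygen uptake 16 (SD 4), walk distance 400 (SD 90), 40 per group, simulated.
- No true effect, CPX shares 50% versus 70%: the t test rejects in about 41% to 44%, Mann–Whitney in about 33% to 35%. At 70% versus 90%: about 60% and about 34%.
- True effect 0.626 SD, equal shares of 50% or 70%: power is about 6% to 10% (t test) or 26% to 33% (Mann–Whitney).

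**5. The stratified alternative.** Within each test, the standardised difference has variance of about 1/n₁ + 1/n₀, so its inverse-variance weight is n₁n₀/(n₁ + n₀).
- Equal 50% shares: 20×20/40 + 20×20/40 = 20, the same information as 40 versus 40 on one test. Power = Φ(0.626·√20 − 1.960) = 80%.
- Shares of 50% versus 70%: 20×28/48 + 20×12/32 = 11.67 + 7.50 = 19.17. Power = Φ(0.626·√19.17 − 1.960) = 78%.
- Simulation with SDs estimated from the data gave about 5% to 6% error under no effect and 76% to 80% power.

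**The case against.** The strongest defence has four parts.

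- **Disclosure.** The authors report the inconsistency themselves and say it may cost power. That is to their credit, but it does not define the endpoint, the sample size is not adjusted for it, and the error rate is not mentioned.
- **Peak oxygen uptake looks like the lead measure.** The sample size uses it, and Setting of Endpoints later describes exercise tolerance by it. This is a fair inference, but it leads to Reading B and its power loss, and the endpoint sentence still gives the walk test as an alternative.
- **An analysis plan may supply the rule.** It may, and the multiplicity result is conditional on no such rule existing. Which measure is primary, however, belongs in the endpoint definition, and the published definition and published sample size do not match.
- **Some patients may have both tests.** Data Collection lists both at admission and at 2-3 months. That would raise the CPX share, but Strengths and Limitations says CPX cannot be done at all institutions.

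A reader might go further and infer that oxygen uptake and metres will be put into one t test, so that a different test mix creates a false effect. Data Analysis does not say this. It speaks of continuous variables, which can equally mean each measure tested separately, and the warning about compatibility argues against raw pooling. Nothing shows that CPX shares differ between the groups, since the source institutions of the controls are not given. A reader might also extend the point to the secondary endpoint that allows either BNP or NT-proBNP; how assays are handled for one secondary endpoint is ordinary analysis-plan detail.

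**Conclusion.** The point stands as a badly fixed primary endpoint. Two tests with success on either give a familywise error of up to 9.75%; that maximum needs only the assumption of independence, and correlation lowers it. Peak oxygen uptake alone gives less than the stated 80% power at 40 evaluable per group unless every patient has CPX: about 65% at an assumed 70% share and about 51% at 50%. The pooling figures apply only if raw values are pooled, and they rest on assumed means, SDs and shares.

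It would be tempting to conclude that the trial cannot answer its primary question. The documents do not support that. Under separate tests the harm is a moderate inflation of error and lower power per test, and an analysis that uses all patients and restores the stated error rate is available.

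**What to change.** State one primary analysis. Compare remote rehabilitation with control only within the same test, standardise each result by a within-test SD defined in advance, and combine the CPX and walk-test strata by inverse variance into a single two-sided 5% test. State which result counts for a patient who has both. Fix this before outcomes are compared with the historical controls.

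The cost is wording and analysis, with no new data. The downside is an effect in SD units, so report peak oxygen uptake and walk distance separately, in their own units, as supporting results. The roughly 80% power assumes a similar standardised effect on both tests; if the walk test responds less, power falls.

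If peak oxygen uptake alone is named primary instead, make walk distance secondary and restate power for the number of CPX patients expected in each group. This keeps clinical units but costs the power shown above. With 59 patients recruited by March 2021, the end of the stated recruitment period, further enrolment may not recover it.

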### Data Collection

We will also collect the following data upon admission: (1) basic information such as facility name, record date, indications for cardiac rehabilitation, hospitalization date, birthdate, sex, height, weight, and social factors (ie, living alone, living with someone, and institutionalization); (2) patient background, including history of hospitalization for heart failure, underlying heart diseases (ischemic heart disease, heart failure, aortic and peripheral artery disease, valvular disorder, and congenital heart disease), concurrent diseases/complications (hypertension, diabetes, atrial fibrillation, cerebral stroke, peripheral vascular disease, chronic kidney disease, anemia, chronic obstructive pulmonary disease, and smoking); (3) treatment history (before hospitalization), including percutaneous coronary intervention, coronary artery bypass grafting, pacemaker placement, and valve surgery; (4) discharge day; (5) vital data (blood pressure and pulse rate); (6) cardiac disease severity in accordance with NYHA classification; (7) clinical laboratory data, including lymphocyte count, hemoglobin, creatinine, sodium, albumin, total bilirubin, uric acid, and BNP or NT-Pro BNP; (8) imaging data, such as electrocardiography, chest radiography, and echocardiography (including left ventricular end–diastolic diameter, left ventricular end–systolic diameter, left ventricular ejection fraction, interventricular septum width, left ventricular posterior wall width, valve lesions, transmitral flow pattern, mitral annular ring early diastole wave, left atrial volume index, and tricuspid regurgitation maximum blood velocity); (9) 6-min walk test and cardiopulmonary exercise testing; (10) questionnaires, health-related QOL scores, and sarcopenia scores; and (11) prescribed drugs. We will collect the following items 2-3 months after discharge (at an outpatient visit): (1) vital data; (2) NYHA classification; (3) clinical laboratory data; (4) imaging data; (5) 6-min walk test and cardiopulmonary exercise testing; (5) questionnaires, health-related QOL scores, and sarcopenia scores; and (6) prescribed drugs. We will also collect the following items 1 year after discharge (at an outpatient visit): all-cause deaths, cardiovascular-related deaths, and hospitalization due to cardiovascular disease (except for planned hospitalization).

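### One-year deaths and cardiovascular hospitalizations are tied to an outpatient visit, which cannot capture deaths or non-attenders and may not be comparable with record-based historical controls

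*Protocol article*

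**What the plan says.** - **Endpoint.** Setting of Endpoints lists as secondary "occurrence rates of clinical events (all-cause deaths, cardiovascular deaths, and cardiovascular hospitalizations". It gives no time point for them.
- **Collection at 1 year.** Data Collection: "We will also collect the following items 1 year after discharge (at an outpatient visit): all-cause deaths", followed by cardiovascular deaths and cardiovascular hospitalizations, with planned admissions excepted. No group is named, and no other source is given for patients who are not seen.
- **Collection earlier.** Setting of Endpoints: "For both groups, various data items will be collected during regular checkups at and 2-3 months after hospital discharge". The 2-3 month list under Data Collection has no event item.
- **Control data.** Strengths and Limitations warns that "background factors may not be accurately aligned with data on the control group, which will be based on clinical records".
- **Control eligibility.** RCR Protocol admits to the control group "those who took cardiopulmonary exercise testing or a 6-min walk test at 2-3 months after discharge".
- **Comparison.** Data Analysis: "The RCR group will be compared with the historical control group at the primary and secondary endpoints", with a chi-square test for categorical variables.

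**The concern.** The article states a setting for the 1-year items, and that setting cannot work for two of the three. A death cannot be observed at a visit the patient would have had to attend. The third item, hospitalization, is lost for anyone who does not come, and patients who have been readmitted or have become frail may be among the least likely to come. Whether an event is recorded can then depend on whether it happened.

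These events are compared with a historical group. Control data are described as record-based, and a chart can show an admission or an in-hospital death without a study visit. If RCR events were taken from the visit and control events from the chart, one endpoint would be measured in two ways.

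The article's aim covers safety as well as efficacy. Deaths and cardiovascular hospitalizations are the only listed endpoint that directly records clinical harm. An event rate that depends on attendance would be weak evidence for that aim, with or without a comparison.

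**Working it through.** **1. The plan's own figure, and what it covers.** Data Analysis says that "a sample size of 67 subjects per group will be required, after allowing for a 40% drop-out rate". The drop-out step reproduces: 40 / (1 − 0.40) = 66.7, rounded up to 67, and 67 × 0.60 = 40.2 evaluable. The calculation is for peak oxygen uptake, which is measured at 2-3 months. The 40% is therefore not a 1-year non-attendance rate and is not used as one below.

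**2. Is another source of events named?** The time point is already given as 1 year after discharge, so the parenthesis adds the setting. The 2-3 month items carry the same parenthesis, but those are vital signs, laboratory values, imaging, exercise tests and questionnaires, which are ordinarily obtained in person. Deaths are not. Nothing in the article mentions record review, telephone contact or family contact for RCR patients, or gives the denominator for event rates.

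**3. Size if the rate is taken among attenders (all inputs assumed).** Let p be the true 1-year risk of any event, a0 the attendance of patients without an event and a1 that of patients with one.

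Observed rate = p·a1 / [p·a1 + (1 − p)·a0]. With p = 0.20 and a0 = 0.70:

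| a1 | Calculation | Observed rate |
|---|---|---|
| 0.35 | 0.070 / (0.070 + 0.560) | 11.1% |
| 0.50 | 0.100 / (0.100 + 0.560) | 15.2% |
| 0.70 | 0.140 / (0.140 + 0.560) | 20.0% |

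A low a1 does not need reluctant survivors. If a share s of patients with an event die and the rest attend at 70%, then a1 = (1 − s) × 0.70. This is 0.35 at s = 0.50 and 0.525 at s = 0.25.

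In the 59 patients recruited by March 2021, 0.20 × 59 = 11.8 true events would be recorded as 11.8 × 0.35 = 4.1 or 11.8 × 0.50 = 5.9.

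**4. Size if all patients stay in the denominator and only RCR deaths are missed.** Take 67 patients, with deaths assumed to be 25% to 50% of events. Recorded events = 67 × p × (1 − s).

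- p = 0.05: 3.4 true events, 2.5 (s = 0.25) to 1.7 (s = 0.50) recorded.
- p = 0.20: 13.4 true events, 10.1 (s = 0.25) to 6.7 (s = 0.50) recorded.

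**5. The opposing effect.** Controls must have been tested at 2-3 months, so they cannot contribute a death before the test. Assume a constant hazard and a 1-year death risk q. The share of 1-year deaths falling in the first m months is [1 − (1 − q)^(m/12)] / q.

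- m = 2, q = 0.05: 0.0085 / 0.05 = 17%.
- m = 3, q = 0.20: 0.0543 / 0.20 = 27%.

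So about 17% to 27% of 1-year deaths could occur in the RCR group but not in the control group. This works against RCR, whereas the losses in steps 3 and 4, if confined to RCR, would work in its favour.

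**The case against.** The strongest reply is that the literal reading is one no site would follow. Listing all-cause death as an item shows an intention to capture deaths. The parenthesis may be shorthand for the follow-up occasion, as at 2-3 months. RCR patients come from institutions that treated them as inpatients, so they have charts too. Tracing of non-attenders is a detail that a journal article may leave to the full protocol, and collection at 1 year would ordinarily cover earlier events, so the absence of an event item at 2-3 months matters little by itself.

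Much of this stands. Silence on tracing alone would be no finding, and nothing in the article says that non-attenders are dropped or counted as event-free. What remains is that the article does not stay silent: it names a method, and that method is unsuitable for deaths. If record review was meant, the sentence should say so.

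A reader might go further and infer that RCR events are under-counted by a rule that differs between the groups, in favour of RCR. The article does not support that:

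- The 1-year sentence names no group. A group-specific rule is only inferred from the remark that control data rest on clinical records, and the one collection rule stated for both groups refers to the same checkups.
- Records can also miss deaths and admissions elsewhere among controls.
- The control eligibility criterion works the other way (step 5).

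**Conclusion.** The point holds as a defect in the stated method of ascertainment for a secondary endpoint. An outpatient visit cannot capture deaths and misses non-attenders, and no other source is named. RCR events may be under-counted, and ascertainment may not be comparable with that of the historical controls. Neither an actual under-count nor its net direction is established.

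The size is illustrative only, because the article gives no event or attendance rate. On the assumed inputs, a true 20% would appear as 11% to 15% among attenders, and as 20% if attendance did not depend on the event. The 40% drop-out allowance lends no support to these attendance rates. The primary endpoint is not affected.

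**What to change.** For the 1-year items, replace the outpatient-visit parenthesis with wording to this effect: vital status and unplanned cardiovascular hospitalizations, with dates, are ascertained by medical-record review as the first source, over the same window in both groups. RCR patients not seen are contacted by telephone or letter. This applies whether or not the patient completed RCR, unless consent is withdrawn.

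For the analysis:

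- Keep every enrolled RCR patient in the denominator, and count untraced patients up to the date last known alive.
- Compare events from the same starting point in both groups, for example with a sensitivity analysis that counts only events after the 2-3 month test among patients alive then.

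The cost is small: one sentence in the protocol and the case report form, and a record check, with a call or letter where needed, for 59 (recruited) to 75 (planned) RCR patients at 2 or 3 per institution, plus the same window for control records. Recruitment ran from January to March 2021. If discharge was close to enrolment, most 1-year follow-up fell after the article's publication in October 2021. The downside is that the reported RCR event rate may be higher.

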### Data Analysis

The analysis will be performed as follows: data on the primary and secondary endpoints of the RCR and control groups will be expressed as mean (SD) or median (quadrant) values. JMP software (SAS Institute) will be used for statistical analysis. Continuous variables will be analyzed using a 2-tailed independent samples *t* test and the Mann–Whitney *U* test. For categorical variables, a chi-square test will be conducted. The RCR group will be compared with the historical control group at the primary and secondary endpoints. The sample size was calculated on the basis of the following estimation. The sample size has been estimated from the data of peak oxygen consumption. A difference in peak oxygen consumption, which is considered clinically relevant, will be in accordance with that reported previously [23,24]. Setting the 2-sided significance level at 5% and power at 80%, a sample size of 67 subjects per group will be required, after allowing for a 40% drop-out rate. Considering these issues, 3 cases are planned to be assigned to each institution (total 75 cases). The level of statistical significance will be set at *P*<.05.

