**Objective:**

This study aims to ascertain the safety and efficacy of remote cardiac rehabilitation (RCR) in the recovery phase in patients with cardiovascular disease.

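### The chi-square difference test planned for clinical events cannot by itself support the stated safety aim, and the study was not sized for events

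*Protocol article*

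**What the plan says.** The abstract's objective reads: "This study aims to ascertain the safety and efficacy of remote cardiac rehabilitation (RCR) in the recovery phase in patients with cardiovascular disease". The title, the Introduction and the Discussion (Aim of This Trial) also name safety alongside efficacy.

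The harm outcomes among the listed endpoints are secondary (Setting of Endpoints): "occurrence rates of clinical events (all-cause deaths, cardiovascular deaths, and cardiovascular hospitalizations"). Data Collection records them at 1 year after discharge.

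Data Analysis then says three things that together determine how they are handled:
- "The RCR group will be compared with the historical control group at the primary and secondary endpoints".
- "For categorical variables, a chi-square test will be conducted".
- "The level of statistical significance will be set at" P<.05.

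On size, the same section says: "The sample size has been estimated from the data of peak oxygen consumption". It arrives at 67 per group after a 40% drop-out allowance, and plans 75 RCR patients. The article gives no expected event rate, no actual size for the historical control group, and no confidence interval or acceptable excess for events.

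Under RCR Protocol, a patient qualifies as a control only after taking a cardiopulmonary exercise test or 6-min walk test at 2-3 months after discharge.

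**The concern.** The test and the aim do not match. A chi-square test asks whether the data contradict equal event rates. A safety conclusion needs the opposite: evidence that any excess of events is smaller than some size that matters. The test has three possible outcomes: significant harm, significant reduction, or P≥.05. Only the third is a likely companion to a favourable safety statement, and it does not carry that meaning.

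The sample size does not fill the gap, because it was chosen for a continuous exercise measure. If deaths and cardiovascular hospitalizations are uncommon, P≥.05 is a likely result even when RCR raises them materially. A report of no significant difference in events could then be taken as support for the wider use that the Discussion foresees.

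**Working it through.** **1. The plan's own figure.** 67 per group after 40% drop-out fits 40 evaluable per group: 40/(1 − 0.40) = 66.7, rounded up to 67. At two-sided 5% and 80% power, 40 per group implies a standardized difference of (1.960 + 0.842) × √(2/40) = 0.63 in peak oxygen consumption. The article gives neither the difference nor the SD, so 67 can only be back-solved. No event rate enters the calculation.

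**2. Inputs for the event test.** From the article: chi-square, two-sided 5%, 75 planned RCR patients, 67 per group required. Assumed, because the article is silent: control event risk p of 5, 10, 15 or 20%; true RCR risk 2p; control group of 67, 75, 150 or 300.

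**3. Method.** For x_R events in n_R RCR patients and x_C events in n_C controls,

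Z = (x_R/n_R − x_C/n_C) / √[p̄(1 − p̄)(1/n_R + 1/n_C)], where p̄ = (x_R + x_C)/(n_R + n_C).

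This is the uncorrected Pearson chi-square in signed form. Harm is detected when Z > 1.96. The miss rate is 1 minus the exact binomial probability of that region.

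Hand check at 75 vs 75, 10% to 20%: power ≈ Φ{[0.10 − 1.96√(2 × 0.15 × 0.85/75)] / √[(0.10 × 0.90 + 0.20 × 0.80)/75]} = Φ{(0.100 − 0.114)/0.0577} = Φ(−0.25) = 0.40. The miss rate is about 60%; exact enumeration gives 59%.

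**4. Miss rate for a true doubling (exact).**

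| RCR vs control | 5%→10% | 10%→20% | 15%→30% | 20%→40% |
|---|---|---|---|---|
| 67 vs 67 | 81% | 64% | 45% | 28% |
| 75 vs 75 | 78% | 59% | 40% | 23% |
| 75 vs 150 | 70% | 46% | 26% | 12% |
| 75 vs 300 | 61% | 36% | 17% | 6% |

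The miss rate crosses 50% at a control rate of about 12% with 75 per group and about 14% with 67 per group. For 80% power to detect a doubling, the normal approximation needs 435 per group at 5% vs 10%, 199 at 10% vs 20%, and 82 at 20% vs 40%.

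**5. What P≥.05 can conceal.** Suppose 16/75 events are observed against 8/75, an observed doubling. Then p̄ = 24/150 = 0.16, the standard error is √(0.16 × 0.84 × 2/75) = 0.0599, and Z = 0.1067/0.0599 = 1.78, which is not significant.

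Now suppose the counts are equal, 8/75 vs 8/75 (10.7% each). The Wilson limits for each group are 5.5% and 19.7%. The Newcombe upper limit for the difference is √[(0.1966 − 0.1067)² + (0.1067 − 0.0550)²] = 0.104. An excess of about 10 percentage points is not excluded even though the observed rates are identical.

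**6. Comparability of the counting period.** Controls had to reach and take the 2-3 month test, so none can have died before it. RCR patients carry no such condition. Events counted from discharge would therefore include early RCR deaths with no possible control counterpart, whichever test is used. The miss rates in step 4 assume an unbiased comparison and do not reflect this.

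**The case against.** **No passage says that P≥.05 will be read as safe.** A reader might infer that the plan rests its safety conclusion on non-significance. The documents do not support that. The chi-square test is named generically for categorical variables, clinical events are not labelled safety endpoints, and the Discussion describes safety during exercise as ensured by monitoring. Safety could be reported descriptively. This objection stands, and it limits the point to what the stated test can and cannot support.

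**The article condenses a fuller protocol.** Intervals or thresholds may sit there, so their absence here is not in itself a defect. That also stands. What remains is that the method the article does name does not answer the safety question.

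**A reader might infer that the study would usually miss a doubling of events.** This is not established. It fails at control rates of 15 to 20% with 67 to 75 per group, and at 10% with 150 or more controls. Patients with heart failure or recent cardiac surgery are eligible, and cardiovascular hospitalization is counted to 1 year, so nothing in the article places the rate below the threshold.

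**Applying the 40% drop-out to the planned event test would overstate the problem.** Taking both groups down to 40 raises the miss rates to 86, 75, 63 and 50%. But the allowance was made for peak oxygen consumption, patients without an exercise test may still have events recorded, and controls are selected for having completed the test. Those figures are not relied on here.

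**Conclusion.** The point holds in a limited form. The chi-square difference test at P<.05 cannot by itself support the safety aim, and this does not depend on any assumed rate. The study was sized on peak oxygen consumption only.

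The size of the problem is conditional on two quantities that the article does not state, the control event rate and the number of controls. The miss rate for a doubling runs from 81% (5% control rate, 67 vs 67) to 6% (20% control rate, 75 vs 300). It is a serious weakness if events are uncommon and a modest one if they are frequent and controls are numerous. Death taken alone cannot be more frequent than death and hospitalization combined, so power to detect a doubling will be lowest for the mortality endpoints.

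This should be changed, as a matter of analysis and interpretation for secondary endpoints. It does not affect the primary analysis.

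**What to change.** In Data Analysis, for each clinical-event endpoint:

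1. Report the RCR event proportion with its exact (Clopper-Pearson) 95% confidence interval, and the RCR-minus-control risk difference with its Newcombe 95% interval.
2. Base any safety statement on the upper limit of the difference, that is, the largest excess not excluded. State that P≥.05 will not be interpreted as showing safety.
3. State that the study was sized for peak oxygen consumption and not for events.
4. For the comparison with controls, count events in both groups from the 2-3 month test onward, among patients who completed it. Report earlier RCR events descriptively, with their proportion and exact interval.

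The cost is a few sentences and two intervals per endpoint, with no extra patients. The date of each event relative to the 2-3 month test is needed in both groups. There are two downsides. The safety statement becomes weaker: 8/75 vs 8/75 would have to be reported as leaving an excess of about 10 points not excluded. Starting at the test also removes RCR patients who did not complete it. If the 40% allowance applied to them, about 45 of 75 would remain (75 × 0.60), and the interval would widen accordingly. Step 1 does not itself set an acceptable excess. If the sponsor wants a pass-or-fail safety conclusion, that limit has to be fixed and justified before the event data are examined.
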